### Control group

The participants randomised to the control group will receive the standard of care treatment offered by the specific clinic where they receive their HAART medication. They will be given a two-page information sheet on healthy living for PLHIV and encouraged to follow this advice. In the event that they are referred for rehabilitation by their clinic nurse or doctor, this will be conducted by a qualified physiotherapist at the study hospital’s physiotherapy department. Participants in the control group will receive a monthly phone call from one of the four lay health workers involved in the HBR intervention. These phone calls will serve to determine their health status and whether their contact/address details have changed. The phone call in the last month will also be utilised to set up a date and time for their post-intervention assessment at the study hospital. On completion of this study, should the HBR intervention be found to be effective, participants in the control group will be offered the opportunity to receive this intervention, at no cost to themselves.

### Blinding

The four lay health workers who will be involved in the HBR intervention are different individuals than the five lay health workers who are employed to conduct the pre- and post-intervention assessment. These latter five individuals will be blinded (at the post-intervention assessment) to the group allocation of participants in order to limit bias. Due to the nature of the intervention, double blinding was impossible, as participants will know whether they are receiving the intervention or are in the control group.

### Ethical considerations

Permission to conduct the study was obtained from the chief executive officer of the study hospital.Ethical approval from the University of Kwazulu-Natal’s Biomedical Research Ethics Committee (BFC052/15) was received on 11 September 2014.This study is registered with the South African National Clinical Trial Register (SANCTR); registration number: NHREC# 4094 as well as the South African Department of Health (DOH number: DOH-27-0715-5094).Participants will be given an information sheet outlining the nature and requirements of the study and their completely voluntary participation, with the right to withdraw at any point during the study. Following this, they will be required to sign a consent form to participate in the study.During all assessments requiring verbal discussion, participants will be interviewed in private locations at the study hospital in order to maintain privacy and confidentiality.A physician at the study hospital must be informed of when the Six Minute Walk Test assessments will be performed and immediately called should participants suffer any adverse response during or after the walk.Any participants who require any medical assistance directly related to the rehabilitation intervention will be immediately referred to the study hospital for assessment and treatment.Participants in the control group will be offered the HBR intervention, should it prove to be beneficial.While no inducements will be offered to participants, their transport costs to and from the study hospital will be covered. A small allowance for food will also be provided to participants for each of their two visits to the study hospital.Participants will be assigned codes in order to maintain their anonymity. No information regarding their involvement in this study will be divulged at any point.All information obtained from participants will be kept under lock and key and electronically on a password protected computer at the UKZN department of physiotherapy for 5 years, after which time all study data will be destroyed or deleted.

### Data analysis

Statistical analysis of collected data will be performed with the assistance of a qualified statistician, employed by the UKZN School of Health Sciences. This statistical analysis will be performed on an intention-to-treat basis. This form of analysis requires participants to be included even if they did not fully adhere to the protocol. The rationale for this approach is that, in this study, it is important to estimate the effects of allocating an intervention in practice, not only the effects in the subgroup of the participants who adhere to it. Descriptive statistics, such as mean and mode, will be used to evaluate baseline demographic data. Analysis of changes between the intervention and control groups will be compared using analysis of variance (ANOVA) and/or analysis of covariance (ANCOVA), determined by the consulting statistician. Level of significance will be set at *P* ≤ 0.05 with confidence intervals set at 95 %. The Statistical Package for the Social Sciences (SPSS) version 22 will be employed to record and analyse the study data.

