### Sample size

The sample size for this study has been calculated based on the group of participants from the HIV-LIVE cohort study who scored for limitation in the mobility-related questions (S1 and S7) of the WHODAS 2.0 (12 item version) tool. The effect size was chosen for these parameters. This was set at an alpha level 0.05 and allowed for a 40 % drop-out rate as indicated in previous studies (power of 80 %). A sample size of 80 participants is required, based on these parameters.

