### Randomisation and follow-up of participants

Following the pre-intervention assessments, participants will be randomly assigned to either the intervention group or a control group (standard care). Computerised randomisation and stratification (according to gender) will be employed in order to ensure homogeneity between intervention and control groups. This will be achieved using the randomise list [RAND()] function in the Microsoft Excel (2013) software package [27]. This will also satisfy allocation concealment, thus ensuring that the investigators will be unaware of to which group each participant will be allocated [28]. In the week immediately following the 16-week HBR intervention, participants from both intervention and control groups will return to the study hospital. The same four outcome measures will be assessed at this follow-up visit in order to ascertain the change from the pre-intervention measures.

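### The between-group test is left open between ANOVA and ANCOVA, with no rule for which result counts; one baseline- and gender-adjusted ANCOVA should be fixed for each outcome

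*Protocol article*

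**What the plan says.** The only sentence in the protocol article on how the groups are compared is in Data analysis. Its subject is "Analysis of changes between the intervention and control groups", and these "will be compared using analysis of variance (ANOVA) and/or analysis of covariance (ANCOVA), determined by the consulting statistician". The section sets the significance level at 0.05 with 95% confidence intervals. It does not say when or on what basis the statistician chooses, whether the choice is made blind to outcome data, or which covariates an ANCOVA would contain. The Blinding section covers the outcome assessors only.

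The section on randomisation and follow-up supplies two relevant facts. Each outcome has a baseline value: "The same four outcome measures will be assessed at this follow-up visit in order to ascertain the change from the pre-intervention measures". Allocation is balanced on one factor: "Computerised randomisation and stratification (according to gender) will be employed". Gender is not mentioned again in Data analysis. No primary outcome is singled out, so the open choice applies to all four measures.

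**The concern.** Leaving model detail to an analysis plan is normal in an article. This text does something else: it states a rule, and the rule is that either method or both may be used at one person's discretion. Two things follow.

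- **Efficiency.** With one baseline and one follow-up value per participant, ANOVA of changes (the same test as group-by-time in a two-point repeated-measures ANOVA) gives the baseline a fixed weight of 1. ANCOVA estimates that weight from the data. To the usual large-sample approximation ANCOVA is never worse, and it is clearly better when the correlation is moderate. In a trial of 80 with a 40% drop-out allowance, the difference is worth having.
- **Error control.** If two tests may be run on the same outcome and nothing says which one decides, the stated 5% is not guaranteed.

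**Working it through.** **Inputs from the documents.** From Sample size: total 80, 40% drop-out allowance, 80% power and alpha ("This was set at an alpha level 0.05"). No numerical effect size, SD or correlation is given; the section says only "The effect size was chosen for these parameters". The figure of 80 therefore cannot be reproduced forward, but the comparison below does not depend on it.

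**Assumptions.** 1:1 allocation, two-sided testing, equal SD at baseline and follow-up, r from 0.5 to 0.7, and a true effect of 0.5 SD.

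**Completers.** 80 × (1 − 0.40) = 48, or 24 per arm. This is the case in which the whole allowance is used.

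**Step 1: variance.** In units of SD², the residual variance is 2(1 − r) for ANOVA of changes and 1 − r² for ANCOVA. The ratio is (1 − r²) / [2(1 − r)] = (1 + r)/2.

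**Step 2: power and detectable effect.** Power is that of a two-sample t-test with 24 per arm and standardised effect 0.5/√v, where v is the residual variance. With 24 per arm, 80% power needs 0.826 residual SDs, so the detectable effect is 0.826 × √v.

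| r | v, changes | v, ANCOVA | ratio | power, changes | power, ANCOVA | detectable, changes | detectable, ANCOVA |
|---|---|---|---|---|---|---|---|
| 0.5 | 1.00 | 0.75 | 0.75 | 40% | 50% | 0.83 SD | 0.72 SD |
| 0.6 | 0.80 | 0.64 | 0.80 | 48% | 56% | 0.74 SD | 0.66 SD |
| 0.7 | 0.60 | 0.51 | 0.85 | 59% | 66% | 0.64 SD | 0.59 SD |

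At r = 0.6, ANOVA of changes needs 1/0.80 = 1.25 times as many completers as ANCOVA for the same precision. Outside this range the gap is wider at low r (30% against 43% power at r = 0.3) and narrower at high r (77% against 81% at r = 0.8).

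**Step 3: type I error if the better test is reported.** In 20,000 simulated null trials per r, with 24 per arm and a gender effect of 0.5 SD, rejecting when either change-score ANOVA or baseline-adjusted ANCOVA reached 5% gave 7.2%, 7.0% and 6.7% at r = 0.3, 0.5 and 0.7. A separate run without a gender effect gave 6.7% to 7.1% for r from 0.5 to 0.7. A single ANCOVA adjusted for baseline and gender gave 5.0% to 5.2%.

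**Step 4: gender.** Assume gender explains 10% of the variance at both visits, with r the overall correlation.
- At r = 0.5, ANCOVA residual variance without gender is 0.75. With gender it is 0.90 − 0.40²/0.90 = 0.722. The ratio of interval widths is √(0.75/0.722) = 1.019.
- At r = 0.7, the values are 0.51 and 0.90 − 0.60²/0.90 = 0.50, so the ratio is √(0.51/0.50) = 1.010.

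Leaving gender out of the ANCOVA thus widens the interval by 1% to 2%. In the simulation of Step 3 the type I error without gender was 4.7% to 5.0%, which is level or slightly conservative.

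**The case against.** The strongest reply is that this is a condensed article, that an analysis plan not shown here may settle the model, and that each method holds 5% if chosen in advance. The last part stands: neither test is invalid. The first part stands only partly. An unseen plan may well name one model, but it would then have to override wording that expressly permits both, so the wording needs correcting either way.

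A reader might also infer four stronger things that the documents do not support.

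- **That the choice will follow the results.** The text gives the choice to the statistician. It does not say that outcome data will be seen first or that the smaller p-value will be reported. The 7% is what the wording allows, not a forecast.
- **That the alternative to ANCOVA is ANOVA of follow-up scores alone.** That comparison would make the loss look larger. But Data analysis speaks of changes, and the follow-up visit is there to measure change from baseline, so change-score ANOVA is the right comparator.
- **That selecting participants on a WHODAS mobility limitation makes regression to the mean a particular threat.** Selection precedes randomisation and acts on both arms alike, so it does not make a chance baseline difference between arms more likely.
- **That the plan excludes adjustment for gender.** It names no covariates, so adjustment is unstated, not ruled out, and the cost of omitting it is small.

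Finally, 40% is a planning allowance. With better retention, absolute power rises under either model, while the variance ratio (1 + r)/2 stays the same.

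**Conclusion.** The point holds: the plan allows two tests without saying which one decides, and one of them wastes information that the trial already collects. At the assumed r of 0.5 to 0.7, the ANCOVA variance is 15% to 25% lower than that of change-score ANOVA, worth 7 to 10 percentage points of power at 24 completers per arm and a 0.5 SD effect. The possible inflation of type I error, to about 7% per outcome, arises only if both tests are run and the better one is reported. The size of the efficiency gain rests on r, which the documents do not give; its direction does not. Gender adjustment is a minor precision gain that matches the analysis to the randomisation. This is a should-fix: a clear improvement at almost no cost, with no flaw in the validity of either test taken singly.

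**What to change.** Replace the sentence with wording such as: *For each outcome, the follow-up score will be compared between groups by ANCOVA with treatment group, the baseline value of that outcome and gender (the stratification factor) in the model. The adjusted mean difference with its 95% confidence interval will be reported.*

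Strike the ANOVA alternative and the clause that leaves the choice to the statistician. Any ANOVA that is kept should be labelled a sensitivity analysis. Since the WHOQOL-HIV BREF has six domains, state which of its scores enters the model.

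The Trial status section says that recruitment has begun, so date the change and make it before any follow-up data are seen. The cost is one or two sentences; it needs no extra participants, visits or measurements.

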### Outcome measures

The WHOQOL-HIV BREF contains brief demographic questions, followed by 31 questions related to the individual’s perceived quality of life. The short form of the WHODAS 2.0 tool consists of 12 core questions assessing an individual’s perceived level of difficulty in carrying out certain day-to-day activities and participating in social, occupational and educational environments. The RMI is a 15-item assessment tool involving a combination of self-reported and directly observed measures of function, such as transferring from a bed to a chair and walking up and down four steps. Although initially designed to assess the functional ability of stroke patients, it is appropriate for populations with a range of physical disabilities [24]. The 6MWT is a test designed to assess distance walked over six minutes as a submaximal test of aerobic capacity/endurance [25]. The 6MWT will be performed, according to the test standards, indoors along a flat, hard surface in a hall on the study hospital’s premises. The walking course will be 20 metres in length, marked at every one metre. The turnaround points will be marked with cones. Absolute contraindications for the 6MWT include the following: unstable angina during the previous month and myocardial infarction during the previous month. Relative contraindications include a resting heart rate of more than 120, a systolic blood pressure of more than 180 mm Hg, and a diastolic blood pressure of more than 100 mm Hg [26]. Individuals who report absolute contraindications for the trial will not be considered for the trial. Individuals who present with any of the relative contraindications will have these measures taken twice more at 15-minute intervals, and if all of these readings are below the accepted limits, they will be able to continue with the trial. The four outcome measures employed in this study are described in more detail in Table 2.

**Table 2 Tab2:** Study outcome measures

Measure	Description
RMI	Assesses functional mobility in gait, balance and transfers. Consists of 14 self-reported items and one direct observation item, with items progressing in difficulty.
6MWT	This test measures the distance that a patient can quickly walk on a flat, hard surface in a period of 6 minutes. It evaluates the global and integrated responses of all the systems involved during exercise.

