WHODAS 2.0 (12 item)	This is a self-reported assessment instrument for health and disability, directly linked to the ICF, used across all diseases. This 12-item version focuses primarily on activities of daily living and participation.
WHOQOL-HIV-BREF	This self-reported instrument, adapted for PLHIV, examines an individual’s perceptions of his/her quality of life across six domains: physical, psychological, independence, social, environment and spirituality.

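### Four unranked outcomes share one unadjusted 0.05 level, and the plan does not say which of them, or how many, decide whether the programme is effective

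*Protocol article*

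**What the plan says.** The Research question, Aim and Objectives sections of the protocol article list perceived disability, quality of life, functional mobility and functional capacity side by side, with one effect objective for each. The Outcome measures section assigns an instrument to each construct and ranks none: "The four outcome measures employed in this study are described in more detail in Table 2". Table 2 adds that the WHOQOL-HIV BREF covers "quality of life across six domains: physical, psychological, independence, social, environment and spirituality".

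The Data analysis section compares changes between arms by ANOVA and/or ANCOVA and states "Level of significance will be set at" P ≤ 0.05, with no split, order or adjustment. The Sample size section refers to people who "scored for limitation in the mobility-related questions (S1 and S7) of the WHODAS 2.0 (12 item version) tool" and says only that "The effect size was chosen for these parameters". It gives no figure for the effect and names no outcome as the one powered.

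Three places rely on an overall verdict. The hypothesis at the end of the Background expects benefit on all four constructs and concludes that the programme is an effective alternative to institution-based rehabilitation. The Control group section says that "should the HBR intervention be found to be effective, participants in the control group will be offered the opportunity to receive this intervention". The Ethical considerations section repeats that offer, conditional on the programme proving beneficial.

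**The concern.** A trial that will be declared effective or not needs a stated rule for that declaration. Here there are four candidate outcomes, one significance level, and no statement of which results count.

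Two things follow. If the reader, or the investigators after the fact, treat any one significant outcome as success, the 5% level no longer describes the chance of a false claim. And if the results are mixed, for example a gain on the 6MWT and none on the WHODAS, the document cannot say whether the trial succeeded or whether the offer to controls is triggered.

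**Working it through.** **The plan's own figure.** The total of 80 cannot be reproduced, because no effect size or SD is stated. The inputs given are alpha ("This was set at an alpha level 0.05 and allowed for a" 40% loss) and the loss and power ("drop-out rate as indicated in previous studies (power of 80" %). Assuming 1:1 allocation, a two-sided test and loss applied as N × (1 − 0.40):

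- Completers: 80 × 0.60 = 48, or 24 per arm.
- Implied standardised difference: (1.960 + 0.842) × √(2/24) ≈ 0.81.

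This is back-solved and is not a figure from the document. It is used below only to show what adjustment would cost.

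**Chance of at least one false positive, if any one of four outcomes were enough.** Inputs: k = 4 (Outcome measures section) and 0.05 per test (Data analysis section). Two-sided tests are assumed; with two groups the ANOVA F test is non-directional.

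- Either direction, independent: 1 − 0.95⁴ = 18.5%.
- Favouring the programme only, independent: 1 − 0.975⁴ = 9.6%. The comparison for a single test is 2.5%.
- Upper limits under any dependence: 4 × 0.05 = 20% and 4 × 0.025 = 10%.

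The document gives no correlations, so a range is shown. It comes from simulating four equally correlated normal test statistics (600,000 draws):

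| Correlation | Any direction | Favouring the programme |
|---|---|---|
| 0 (exact) | 18.5% | 9.6% |
| 0.3 | 17.4% | 8.8% |
| 0.5 | 15.5% | 7.8% |
| 0.7 | 13.0% | 6.5% |

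**If all four had to be significant.** The chance that all four are significant cannot exceed the chance for any one of them, so error stays at or below 5% (2.5% in the favourable direction). Power falls instead. With 80% power on each outcome and independence it would be 0.80⁴ = 41%; positive correlation would bring it nearer to 80%.

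**Cost of the alternatives at the implied 0.81 SD.**

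- One primary at 0.05: 80% power with 24 completers per arm, N = 80.
- Bonferroni over four (0.05/4 = 0.0125): about 62% power with 24 per arm. Restoring 80% needs 35 per arm, or 70 completers, and 70/0.60 gives 117 randomised.

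**The case against.** The strongest reply is that the document never says one significant outcome is enough. The Background hypothesis joins the four constructs with a conjunction, and if all four are required nothing is inflated. Alternatively, the Objectives can be read as four separate questions, each answered at its own 5% level. Both readings are possible. What stands is that the article chooses none of them while still hanging a single decision on the outcome.

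A second reply is that multiplicity methods are commonly left to an analysis plan that is not shown. That is fair for the choice of adjustment, and the lack of one is not held against the article by itself. It does not cover the missing primary outcome. That is a protocol-level choice, because the sample size and the conclusion both depend on it, and the article covers outcomes, sample size and analysis without making it.

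Three stronger readings are tempting and are not supported:

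- A reader might count nine tests (three scales plus six WHOQOL domains) and quote 1 − 0.95⁹ = 37.0%. Table 2 describes what the instrument covers; nothing says the domains are tested separately, and there is one quality-of-life objective. The rate would be higher than for four tests if they were, but that is conditional.
- A reader might take 18.5% as the chance of wrongly declaring benefit. It includes results that favour control; the figure for benefit is about 9.6%.
- A reader might infer that the sample size makes the WHODAS total the powered outcome. The Sample size section uses two WHODAS mobility items to identify a source group and stops there.

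**Conclusion.** The point holds in this form: four co-equal outcomes share one unadjusted level, none is primary, and the rule for calling the programme effective is not fixed.

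The size depends on the rule eventually applied. Under an any-one rule, the chance of at least one false positive is up to about 18.5% for independent outcomes and about 13% to 15.5% at correlations of 0.7 to 0.5. In favour of the programme it is up to about 9.6%, nearly four times the 2.5% of a single test. Because these outcomes are likely to be positively correlated, the lower figures are more plausible. Under an all-four rule there is no inflation, only lost power. These results assume two-sided tests and, for the correlated cases, equal correlations.

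The one action the document ties to the verdict is the post-trial offer to controls, but the trial's main conclusion has the same gap. The remedy is cheap, so it should be made before analysis.

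**What to change.** Before any outcome data by arm are seen, issue a dated amendment and registry update that names one primary outcome at the post-intervention visit. State that effectiveness, including the trigger for the offer to controls, is judged on that single test at two-sided 0.05.

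The WHODAS 2.0 12-item total is a reasonable candidate: Table 2 links it to the ICF, the study's framework, and it matches the first effect objective. Against it, it is self-reported by participants who know their allocation, and the Sample size section does not establish it as the powered endpoint. The investigators should justify their choice against the 6MWT, which is a measured distance, and state the effect size that 80 participants can detect on the outcome chosen.

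Treat the other three scales as secondary, either with Holm adjustment across them or as estimates with confidence intervals. Report the WHOQOL domains descriptively.

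The cost is small. N stays at 80 and secondary claims become slightly harder to make. The Trial status section says recruitment has begun, so the timing of the decision must be documented; a change of wording alone is not enough.
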